### Data Collection and Sample Handling

Sample collection was performed independently by participants at home as part of the fully remote study workflow. Final group assignment (CS vs VD) was based retrospectively on the actual mode of delivery at birth. Each participant was asked to provide 3 stool samples at predefined time points: during late pregnancy (T0, from gestational week 32 onward), within 2 to 3 days postpartum (T1), and at 90 (±10) days postpartum (T2). These time points were selected to capture baseline microbiome composition, immediate peripartum changes, and long-term recolonization dynamics. For each time point, participants received a sample collection kit that included a collection tube (DNA/RNA Shield Fecal Collection Tube, Zymo Research), a single-use stool catcher (Feces Catcher, Zymo Research), written instructions, and a prepaid return envelope. Paper-based questionnaires accompanied each sample kit and covered maternal health status, medication use, pregnancy and birth-related variables, and lifestyle factors such as nutrition and physical activity. Participants returned both the stool sample and completed questionnaire in the same shipment. Questionnaires were designed to be completed within approximately 10 minutes and spanned 2 to 3 pages, depending on the time point. Incomplete or missing forms were actively followed up by the study coordinator.

Samples were shipped by standard postal service and received by the coordinating study center. Although the exact time between sampling and mailing was not recorded for all participants, no sample exceeded the manufacturer’s recommended stability window.

Upon arrival, samples were documented and immediately stored in a temperature-monitored, alarm-secured refrigerator at 4°C to 8 °C, where they remained until DNA extraction. The median storage duration was 434 days (range: 137‐784 d), with no deviations from the defined storage conditions. Despite the stabilizing effect of DNA/RNA Shield, the wide range of storage periods may still cause subtle bias.

The nucleic acid stabilization buffer (DNA/RNA Shield) ensures preservation of microbial DNA for at least 24 months at ambient temperature (4° C‐25  °C) and indefinite stability when frozen (<−20 °C), according to the manufacturer. Accordingly, all returned samples were accepted for processing. No exclusions were made due to transport delays, damage, or temperature fluctuations.

DNA extraction was performed using the ZymoBIOMICS 96 MagBead DNA Kit (D4308, Zymo Research) on an automated pipetting workstation (epMotion 5075t, Eppendorf). A slightly modified protocol was applied: 200 µL of fecal sample were mixed with 450 µL of lysis buffer and subjected to mechanical disruption using a bead-beating step in a TissueLyzer (30 Hz; 5 min). DNA was eluted in 50 µL of nuclease-free water and stored at 4 °C to 8  °C until library preparation. For amplification of the V3-V4 region of the 16S rRNA gene, the Quick-16S Next Generation Sequencing Library Prep Kit (D6400, Zymo Research) was used with 341f/806r primers. The protocol was modified by using half reaction volumes and performing 30 polymerase chain reaction (PCR) cycles. No fluorometric quantification was performed prior to amplification; however, postamplification quality control confirmed consistent DNA concentrations across all samples, and no samples had to be excluded due to insufficient yield or quality. Sequencing was conducted on an Illumina MiSeq platform using the MiSeq Reagent Kit v3 (600-cycle, paired-end 301 bp; MS-102‐3003, Illumina). Cluster generation occurred onboard the MiSeq instrument. Pooled libraries were denatured and diluted according to the manufacturer’s protocol and loaded at a final concentration of 12 pM. A PhiX control library (15%) was spiked in to increase run diversity and monitor sequencing quality. Quality controls included 2 extraction blanks consisting of lysis buffer from the DNA extraction kit, one of which was carried through library preparation, and 1 PCR-negative control (nuclease-free water). No spike-in standards for absolute quantification were used. A positive control from the Quick-16S Next Generation Sequencing Library Prep Kit (ZymoBIOMICS Microbial Community DNA Standard) was processed alongside study samples. Mock community controls beyond this kit-derived standard were not included. All study samples and controls were processed and sequenced in a single batch to avoid inter-batch variation.

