### Eligibility and Recruitment

Participants were eligible for inclusion if they were aged at least 18 years, in the third trimester of pregnancy, and planned to deliver either by elective CS or VD without medical indication for peripartum antibiotics. Sufficient German language skills were required to complete the informed consent process and written study documentation. Exclusion criteria comprised participation in another clinical study, chronic inflammatory bowel disease (eg, Crohn disease or ulcerative colitis), hematologic or oncologic disease, chronic renal or hepatic disease, and chronic viral infections such as HIV, hepatitis B virus, or hepatitis C virus. Additional exclusions included systemic use of immunosuppressants, virostatics, cytostatics, proton pump inhibitors, or systemic antimicrobial agents (antibiotics or antifungals) within the past 3 months. Women with a foreseeable need for surgery or antimicrobial treatment other than cefuroxime within the study period (90 days postpartum) were also excluded.

Participants were recruited between May 2022 and October 2023 at 2 German level 1 perinatal centers and affiliated outpatient facilities. Eligible women were identified by attending obstetricians and midwives during routine clinical care. To support recruitment beyond the hospital setting and to address recruiting bias, awareness of the study was raised through posters in clinic waiting areas, printed flyers distributed during antenatal visits, and social media announcements via the official channels of the participating institutions. In addition to reaching a broader population, the social media strategy was specifically intended to include women with low-risk pregnancies who received all prenatal care in the outpatient sector and would otherwise have had limited contact with hospital-based recruitment. This approach aimed to reduce recruitment bias toward high-risk pregnancies, such as those with gestational diabetes, multiple gestation, or prior cesarean delivery. Pregnant women and new mothers represent a population with specific logistical and time-related needs, which informed the choice of a decentralized recruitment and study design.

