Analyses will follow a 2-level structure. First, community-level analyses where ASV-based distance matrices (Bray-Curtis, and weighted and unweighted UniFrac) will be used to assess group differences via permutational multivariate ANOVA [30]. Longitudinal microbiome changes will be evaluated by comparing within-individual distance differences across time intervals using Mann-Whitney *U* tests, visualized via principal coordinates analysis. Second, taxonomic-level analyses, in which higher-rank taxonomic profiles (phylum, genus, and species, where available) are summarized descriptively. Hypothesis testing at the taxonomic level will only be conducted if community-level differences emerge, to avoid overinterpretation of sparse compositional data. Given the modest cohort size, all analyses are designed for hypothesis-generating, exploratory interpretation.

Alpha diversity (Shannon index, observed features, and Faith phylogenetic diversity) and beta diversity (Bray-Curtis, and weighted and unweighted UniFrac) will be calculated to describe within- and between-sample diversity. Group comparisons will be analyzed using the Wilcoxon rank-sum or Kruskal-Wallis tests for alpha diversity and permutational multivariate ANOVA for beta diversity. Differential-abundance analysis will be performed using the Analysis of Composition of Microbiomes II (ANCOM-II) [31], a method developed for sparse compositional microbiome data. Given the modest sample size, differential-abundance findings will be interpreted exploratorily. All downstream analyses and visualizations will be performed in QIIME2 and a Python-based environment (Python Software Foundation). Workflow steps, parameters, and software versions will be version-controlled to ensure reproducibility. In addition to taxonomic data, analyses will integrate metadata on parity, medication use, and dietary habits. Associations between microbiome composition and clinical, lifestyle, or sociodemographic variables will be explored through correlation analyses and, where applicable, multivariate approaches such as redundancy analysis or generalized linear models.

Although DNA/RNA Shield stabilizes microbial nucleic acids, prolonged refrigerated storage before extraction may introduce subtle compositional shifts. This potential source of bias will be considered during interpretation.

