### Statistical Analysis Plan

The following procedures specify how the predefined outcomes will be analyzed. The analysis will follow an exploratory framework. Although simple, biologically plausible hypotheses have been specified, no formal power calculation was performed. Consequently, results will be interpreted as hypothesis-generating rather than confirmatory.

Feasibility outcomes will be summarized descriptively using proportions, medians, and ranges. Timing of sample returns relative to the predefined collection windows (T0, T1, and T2) will be evaluated by calculating time intervals (in d) between the target and actual return dates. These intervals will be summarized using medians and IQR and compared between delivery groups where appropriate. Reasons for loss to follow-up (eg, no sample returned) will be documented, and analyses will be performed on available cases without imputation of missing data. This analysis will help assess protocol adherence and identify potential logistical barriers in the home-based study model.

To address the previously defined microbiome outcomes, the following statistical approaches will be applied: group comparisons between CS and VD will be performed for each time point (T0, T1, and T2) and longitudinally within participants as well as within groups, using all available paired samples (eg, T0-T1 or T1-T2), where applicable. Alpha diversity metrics (eg, Shannon index and Chao1 richness) will be compared using nonparametric tests (Wilcoxon rank-sum or Kruskal-Wallis test). Beta diversity will be evaluated using permutational multivariate ANOVA based on distance matrices (eg, Bray-Curtis and UniFrac). Visualization will include principal coordinates analysis.

Analyses will follow a 2-level structure, with primary community-level testing and secondary, exploratory taxonomic-level summaries.

Relative abundances of microbial taxa at different taxonomic levels will be summarized descriptively.

Exploratory differential-abundance analyses will be performed using ANCOM-II, a method suitable for sparse compositional data that incorporates its own procedures for controlling false discoveries. Taxonomic-level hypothesis testing will only be performed if community-level analyses indicate meaningful group differences.

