At the same time, the implementation of a fully non–site-bound model presented specific challenges. In the VD group, it was difficult to anticipate the exact timing of delivery and thus ensure timely sample collection at T0 and T1. Participants were encouraged to prepare the sampling kit in advance and bring it to the hospital in their birth bag, but adherence to this instruction was not always possible. Additionally, logistical issues were encountered early in the study due to the use of time-limited digital postage codes. As these codes expired before participants mailed their samples, significant mailing delays occurred. The issue was resolved by switching to traditional postage stamps, which ensured reliable sample dispatch without further complications. Although this did not result in sample loss, it created confusion and required additional follow-up communication. These experiences highlight the need for practical guidance and reliable infrastructure when conducting off-site clinical research.

Recruitment was also affected by varying levels of institutional engagement across study sites. While the home-based design reduced participant burden, it still required initial support from clinical staff to initiate contact or distribute study materials. Staff at one study center demonstrated strong interdisciplinary cooperation, with committed medical professionals actively facilitating participant outreach. This differed significantly in the other study center, where limited personnel resources and skepticism about participants’ willingness to provide samples postpartum led to reluctance in supporting recruitment. This ultimately contributed to the premature closure of enrollment before the initially planned sample size was reached. This limitation in institutional support directly impacted the final sample size, which remained below target and unevenly distributed between the 2 study arms. In addition, several participants had to be excluded during the study due to protocol violations, such as postpartum antibiotic use identified retrospectively through questionnaire data, or delayed sample return beyond the predefined protocol windows. Despite these constraints, the sampling scheme captured three critical time points—before delivery, shortly after birth, and during postpartum recovery—enabling the identification of both acute and long-term changes in microbial composition.

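### T0 is not anchored to birth, so T0-T1 covers a variable stretch of late pregnancy, and the planned comparison of within-woman distances across intervals ignores elapsed time

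*Protocol article*

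**What the plan says.** Data Collection and Sample Handling defines T0 as taken "during late pregnancy (T0, from gestational week 32 onward". The other two samples are due "within 2 to 3 days postpartum (T1), and at 90 (±10) days postpartum (T2". The same section gives the purpose: "These time points were selected to capture baseline microbiome composition, immediate peripartum changes, and long-term recolonization dynamics".

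Microbiome Analysis and Bioinformatics Pipeline evaluates longitudinal change by "comparing within-individual distance differences across time intervals using Mann-Whitney" U tests. The Statistical Analysis Plan section adds that longitudinal comparisons are made "using all available paired samples (eg, T0-T1 or T1-T2), where applicable". Neither place names gestational age at T0, days from T0 to birth, or interval length as a term in any analysis.

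Two statements bear on whether T0 timing might differ by group. Under Eligibility and Recruitment, women "planned to deliver either by elective CS or VD without medical indication for peripartum antibiotics" could enter. Under Principal Findings the article reports: "In the VD group, it was difficult to anticipate the exact timing of delivery and thus ensure timely sample collection at T0 and T1".

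**The concern.** T0 is the reference from which the peripartum change is measured, and it is the only one of the three time points without a closed window tied to birth. The Background section holds that pregnancy itself reshapes the gut microbiome toward lower diversity and less stability. On that premise the time between T0 and birth is not inert: a T0 taken eight weeks before delivery carries late-pregnancy change that a T0 taken two days before does not.

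Two readings of the results are exposed:

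- **Interval against interval.** If T1-T2 distances exceed T0-T1 distances, the longer elapsed time may be the whole reason.
- **Cesarean against vaginal delivery on T0-T1 distance.** If one group tended to give T0 earlier relative to birth, that alone could separate the groups.

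The microbiome results are secondary and exploratory, but the article intends them to inform the design of later powered studies, so a timing artefact could be carried forward.

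**Working it through.** The article states no power, error rate or effect size that bears on T0, so there is no figure to reproduce. The check is arithmetic on the stated windows, followed by an illustration on assumed values.

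**Step 1. T1-T2 length.** Inputs: T1 on day 2 to 3, T2 on day 80 to 100 (90 ± 10).
- Shortest: 80 − 3 = 77 days. Longest: 100 − 2 = 98 days. Ratio 98/77 = 1.3.

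**Step 2. T0-T1 length.** Longest = (birth week − 32) × 7 + 3 days. Shortest = 0 + 2 = 2 days, with T0 on the day of birth. Birth weeks are assumptions, because the article gives none.
- Birth at week 37: 5 × 7 + 3 = 38 days
- Week 39: 7 × 7 + 3 = 52 days
- Week 40: 8 × 7 + 3 = 59 days
- Week 42: 10 × 7 + 3 = 73 days

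At the extremes T0-T1 can vary between women by a factor of 38/2 = 19 (birth at week 37) to 73/2 = 36.5 (week 42), against 1.3 for T1-T2. Even the longest T0-T1 here (73 days) is shorter than the shortest T1-T2 (77 days). Comparing the two intervals therefore always sets a shorter one against a longer one. This needs no assumption about delivery mode.

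**Step 3. Could T0-T1 length differ by group?** Simulation with T0 uniform from week 32, mean birth week 38 to 39 for cesarean (SD 0.5 week) and 39 to 40.5 for vaginal delivery (SD 1 week), all assumed:
- T0 taken by week 36 or week 38: median T0-T1 is 0 to 14 days longer in the vaginal group.
- T0 allowed up to birth: the gap is about −1 to +7 days.
- Equal mean birth weeks: the gap is about zero.

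**Step 4. What would a gap do to the test?** The article reports 19 T1 samples in total, so there are at most 19 T0-T1 pairs. With an assumed split of 12 cesarean and 7 vaginal, no true peripartum difference and a two-sided 5% Mann-Whitney test (4,000 runs), the rejection rate by the shift that timing alone puts into the distance is:

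| Shift (SD) | Rejection rate |
|---|---|
| 0 | 4% |
| 0.25 | 7% |
| 0.5 | 15% |
| 1 | 47% |

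The article gives no drift size, so the true position in this range is unknown.

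**Step 5. Do the planned safeguards cover it?**
- The Statistical Analysis Plan section summarises days between target and actual return dates. An open-ended T0 has no target date, and a return date is not a collection date. The article itself reports mailing delays and says that sampling-to-mailing time was not recorded for everyone.
- Conditional adjustment is planned for imbalances in maternal variables, with gestational diabetes as the example. The Discussion lists parity, medication or supplements, diet and allergies. Lead time from T0 to birth is in neither place.

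**The case against.** A reader might infer that T0 timing is tied to delivery mode, and that T0-T1 change is therefore not comparable between the groups. The article does not support that. It gives no T0-to-birth interval and no gestational age at birth for either group. T0 was returned with the signed consent form from a kit sent at inclusion, so its timing may simply follow enrolment date in both groups. The remark about difficulty in the vaginal group gives no direction. The cesarean group also contains two women who had planned vaginal delivery. Vaginally delivering women pass through late pregnancy too, which is part of what a comparator is for. Bias needs both a difference in lead time and material drift after week 32, and neither is shown. All of this stands.

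A reader might also take T0-T1 distance to be the study's main measure of the acute effect. The stated hypotheses on alpha diversity and *C. difficile* are cross-sectional contrasts at T1 and do not use T0. This stands as well.

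The sentence on Mann-Whitney tests is ambiguous. The test is unpaired and would fit a comparison of the two groups within each interval, in which case no test of T0-T1 against T1-T2 was intended. That is a fair reading, but the wording speaks of comparison across intervals and should be settled.

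Finally, the microbiome work is labelled exploratory, residual confounding is expected, and timing may be compared between groups. That lowers the stakes, but none of it measures or uses T0 lead time.

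**Conclusion.** The point holds in a limited form. T0 has no closing limit short of delivery and no anchor to birth, so T0-T1 covers an uncontrolled stretch of late pregnancy: about 2 days up to 38 to 73 days under assumed births at weeks 37 to 42, against 77 to 98 days for T1-T2. A raw difference between T0-T1 and T1-T2 distances cannot be separated from interval length.

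For cesarean against vaginal delivery on T0-T1 distance, bias is conditional on lead time differing by group. That is plausible from the elective cesarean date and the reported timing trouble in the vaginal group, but it is not demonstrated, and its size cannot be derived from the article. The cross-sectional T1 comparisons are untouched. This is a specific weakness in a secondary, exploratory analysis. It could still be corrected, since analysis was reported as ongoing in December 2025.

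**What to change.** 1. Compute days from T0 to birth for each woman from the recorded dates, and tabulate them by delivery group.
2. State that T0-T1 distance is compared between cesarean and vaginal delivery within that interval.
3. Add one sensitivity analysis that either includes T0 lead time as a single covariate or restricts to the range of lead times common to both groups. With at most 19 pairs, several timing covariates combined with a fixed cut-off would ask too much of the data.
4. Report T0-T1 against T1-T2 distances descriptively, with interval lengths alongside, and do not test them against each other.

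The cost is a few lines in the analysis plan and no new sampling. The sensitivity analysis spends one degree of freedom or loses a few pairs. Some collection dates may be approximate, because time between sampling and mailing was not recorded for all participants; the report should say for how many.

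### The statement that no sample exceeded the stability window is not supported by the article's own figures: at least one was stored 53 to 54 days past the 24 months cited

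*Protocol article*

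**What the plan says.** All the relevant statements stand in Methods, Data Collection and Sample Handling, within a few sentences of each other.

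- On shipping, the article concedes that "the exact time between sampling and mailing was not recorded for all participants" and then adds that "no sample exceeded the manufacturer’s recommended stability window".
- On storage, samples were "immediately stored in a temperature-monitored, alarm-secured refrigerator at" 4 to 8 °C and stayed there until DNA extraction. "The median storage duration was 434 days", with a range from 137 days up to "784 d), with no deviations from the defined storage conditions".
- On stability, the buffer "ensures preservation of microbial DNA for at least 24 months at ambient temperature" (given as 4 to 25 °C). Unlimited stability is claimed only for samples frozen below −20 °C.
- The conclusion drawn from the stability figure is: "Accordingly, all returned samples were accepted for processing".

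The section also says that the wide range of storage times could bias results slightly. Microbiome Analysis and Bioinformatics Pipeline repeats this and promises to take it into account in interpretation. Neither place says that any sample passed 24 months.

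**The concern.** The assurance has no stated limit, and the article names only one period that could apply to refrigerated samples. The reported maximum storage time is longer than that period. A reader who relies on the assurance will take every sample to lie within the manufacturer's specification, and the article's own numbers do not bear this out.

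What is at stake is the validity of composition data. The samples were extracted and sequenced as one batch, so a sample's storage time is set almost entirely by when it arrived. The oldest samples come from the first women enrolled and, as shown in the working, should be from late pregnancy or the first days after birth rather than from day 90. If storage did alter composition, the effect would run in parallel with the planned within-person comparisons over time. The sensitivity analyses mentioned in Statistical Analysis Plan are alternative distance metrics or differential-abundance methods; none concerns storage time.

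**Working it through.** **Inputs.** From Data Collection and Sample Handling: assured period of at least 24 months unfrozen; storage at 4 to 8 °C; storage range 137 to 784 days, median 434. From Ethical Considerations and Results: first enrolment May 2022, last sample received March 2024, extraction and sequencing completed October 2024.

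**1. The article's own figure.** The statement implies zero samples over the window, hence a maximum sample age of no more than 24 months. This cannot be reproduced:

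- Two calendar years are 730 or 731 days. 784 − 731 = 53 and 784 − 730 = 54 days over.
- In months, 784 / 30.4375 = 25.8.
- As a share, 54 / 730 = 7.4% and 53 / 731 = 7.3%.
- On the most generous conversion, 24 × 31 = 744 days, and 784 − 744 = 40 days over.

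The unlimited period for frozen samples does not apply, because these were refrigerated. The overrun is a lower bound, since storage is counted from arrival. Time at home and in transit comes on top, and the Discussion (Principal Findings) reports early mailing delays from expired postage codes.

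**2. Is 784 days a plausible figure?** If the last sample arrived between 1 and 31 March 2024 and was the one stored 137 days, extraction fell between 16 July and 15 August 2024. Counting 784 days back gives 24 May to 23 June 2022, which fits first enrolment in May 2022. If extraction instead took place in October 2024, the last sample would have been stored 184 to 244 days, which does not match the 137-day minimum. The 784-day limit would then fall between 9 August and 8 September 2022, so any sample received before it would have an even larger overrun. The dates need reconciling, but neither version removes the conflict.

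**3. How many samples?** The median and range do not give the number. The maximum makes one certain, and the median of 434 days places at least half inside the window. As an assumption only: even accrual of the 31 women with samples over 18 months is 31 / 18 = 1.72 a month, and 54 days is 54 / 30.4375 = 1.77 months, so about 1.72 × 1.77 ≈ 3 women's baseline samples, plus any early postpartum samples that arrived in that time. A range of 1 to 5 of the 71 analysed samples is reasonable under that assumption. The true number could differ.

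**4. Which time point?** With one extraction date, samples over 730 days arrived within 54 days of the oldest one. The final sample is due 80 to 100 days after birth, and hence at least 80 days after the same woman's baseline sample. Unless a baseline sample was mailed very late, samples over 730 days are therefore baseline or early postpartum samples.

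**The case against.** The arithmetic is hard to dispute; the reading of it is not.

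- *The sentence may concern shipping only.* It stands in the shipping paragraph, follows a clause about time before mailing, and precedes the account of storage. That may have been the intent, and a breach of 24 months before arrival is implausible. But the wording has no such limit and no separate transport period is given. The later acceptance of all samples rests on the 24-month figure, which does not cover a sample stored for 784 days.
- *Twenty-four months is a minimum, not an expiry date.* This stands. A sample at 25.8 months is outside the assured period but is not shown to be degraded. A reader might infer that the statement is simply false or that the sample is invalid; the documents support only that the statement lacks support in the figures given.
- *The acceptance rule does not rest on the disputed sentence.* This also stands. The rule follows from the manufacturer's figure. That figure is not shown to be wrong; it just does not reach the longest-stored sample or samples.
- *Storage bias is already disclosed.* In part. The wide range and possible shifts are acknowledged, and both 784 days and 24 months are printed. That the one exceeds the other is not.
- *All samples passed quality control.* The check described was on DNA concentration after 30 amplification cycles, with no fluorometric measurement beforehand. It does not show that composition was preserved, but nor does anything show that it was not.
- *Accrual may have been slow early on.* The second centre was approved only in September 2022, and the median of 434 days lies below the midpoint of the range, (137 + 784) / 2 = 460.5. Both fit a small number of very old samples.

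**Conclusion.** The assurance is not supported by the article's own figures. At least one sample was 53 to 54 days past the period that the manufacturer is said to assure, not counting time at home and in the post. The 24-month figure therefore does not by itself justify accepting every returned sample. This rests only on figures in one section and on reading the assurance as written, without a limit to shipping.

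The consequence is modest. Only one over-age sample is certain, and the article does not say whether it is among the 71 analysed. The feasibility outcomes, which are primary, are unaffected; the microbiome outcomes are secondary and exploratory. A reader might infer that the baseline data are degraded or that the comparison of delivery groups is biased. The documents support neither: no degradation is reported, and nothing shows that the oldest samples differ by delivery group. The point should be corrected, but it does not threaten the study's main conclusions.

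**What to change.** 1. Correct the sentence so that it agrees with the reported storage range. If it was meant for the time before arrival only, say so.
2. From the arrival log, report the number of samples stored for more than 24 months by group and time point. State that the count is a lower bound where the sampling date is missing.
3. Name one sensitivity analysis in Statistical Analysis Plan: repeat the alpha- and beta-diversity comparisons without those samples.
4. While doing this, state the extraction date and reconcile it with the 137-day minimum and the March 2024 last receipt.

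The cost is small. Arrival was documented for each sample and analysis was still under way in December 2025, so this is one sentence, one count and one rerun. The drawbacks are a less favourable statement on sample quality and slightly fewer samples in the sensitivity run.
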